### Statistical analysis

Descriptive statistics using proportions, means and standard deviations will be reported where appropriate. All efficacy outcome measures will be analyzed on an intent-to-treat (last observation carried forward) basis and study completer basis. Results will be presented with 95 % confidence intervals where applicable. Proportions of adverse events will be summarized. All statistical tests will be two-sided using an alpha level of 0.05. Analyses will be adjusted for age and gender when there is a significant difference between the groups at baseline.

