So far little is known about the mechanism behind this effect. Neurobiological research has focused on lithium’s influence on neurotransmitters such as serotonin [9] or noradrenalin and dopamine [10]. Lithium’s influences on the cortisol stress hormone system [11], the γ-aminobutyric-acid [12], second messenger systems such as the inositol metabolism and glycogen synthase kinase 3 have also been investigated [13]. Lithium has demonstrated to have an effect on impulsivity and aggression via several pathways within the nerve cell [14, 15] which is discussed as one of the underlying mechanisms behind the anti-suicidal efficacy.

As suicide research has to deal with specific methodological difficulties the design and development of study protocols needs to be cautious. Ethical and statistical issues need thoughtful consideration.

In 2005, the worldwide first placebo-controlled randomized trial designed specifically to investigate the influence of lithium on suicidal behavior was conducted and published in 2008 by Lauterbach et al. [16]. Survival analysis showed no significant difference in suicidal acts between lithium and placebo-treated individuals (adjusted hazard ratio 0.517; 95 % CI 0.18–1.43); however, post hoc analysis revealed that all completed suicides had occurred in the placebo group accounting for a significant difference in incidence rates (*P* = 0.049). Within a treatment period of one year, no suicides occurred within the lithium group (*n* = 84) compared to three suicides within the placebo group (*n* = 83). No significant differences were found in terms of suicide attempts (seven suicide attempts each in the placebo and lithium group). To date, no study has investigated how fast this anti-suicidal effect appears. It is unclear where in the course of treatment this effect arises.

The primary aim of the present study is to determine whether lithium exerts an anti-suicidal effect through a decrease in suicidal thoughts and/or behavior within the first 5 weeks of treatment. The secondary aim of the study is to determine whether lithium influences suicidal thoughts and/or behavior through the indirect path of improving depressive symptoms, anxiety or impulsivity.

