### Methods/Design

The present study is a multi-center, 4 year, randomized placebo-controlled double-blind trial. Patients with unipolar or bipolar disorder suffering from a major depressive episode with suicidal thoughts and/or behavior according to DSM IV criteria will be randomly allocated to lithium therapy plus treatment as usual versus placebo treatment plus treatment as usual. The hypothesis to be tested is that lithium treatment plus treatment as usual leads to a significant reduction of suicidal thoughts and/or behavior compared to placebo therapy plus treatment as usual within 5 weeks of treatment. The primary end point of this study is the change in Sheehan Suicidality Tracking Scale (S-STS, [17]) between the beginning of treatment and after a treatment episode of 5 weeks. Further endpoint in this study are changes in the Columbia-Suicide Severity Rating Scale (C-SSRS, [18]), the Montgomery Asberg Depression Rating Scale (MADRS, [19]), the Hamilton Anxiety Scale (HAM-A, [20]), the Clinical Global Impression Scale (CGI, [21]) and the Barratt Impulsivity Scale (BIS, [22]) from initial treatment to 5 weeks post treatment. A comparison of total scores in the C-SSRS, MADRS, HAM-A and the Young Mania Rating Scale (YMRS, [23]) within the participating centers will be conducted. In addition, the number and dosage of concurrent medication and number of psychotherapy hours will be explored as secondary endpoint. Weekly changes in the C-SSRS, MADRS, HAM-A and YMRS within the observation period and percentage of days where the S-STS Scale score equals zero will be reported. Two-hundred and fifty-four patients will be included with, thereof 127 in each treatment group. Recruitment started on October first, 2013 and will end on September 30^th^, 2017. Treatment includes 5 weeks of treatment plus 1 week of follow-up. For a detailed description of the inclusion and exclusion criteria, please see Table 1.

**Table 1 Tab1:** In-and exclusion criteria

Inclusion criteria	Exclusion criteria

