### Assessments

#### Clinician administered scales

The Mini International Neuropsychiatric Interview (MINI, [24]) as well as the structured clinical interview for DSM-IV axis II personality disorders (SKID II, [25]) will be used for diagnosis. To assess suicidal thoughts and/or behavior, the Sheehan Suicidality Tracking Scale (S-STS) is used, both as clinician and self-reported. The S-STS scale was selected because it maps directly to the Columbia Classification Algorithm of Suicide Assessment (C-CASA) coding system, endorsed by the FDA. The S-STS evolved from the Suicidality Module of the MINI Structured Diagnostic Interview for DSM-IV and is a prospective self or clinician report scale. The eight item scale assesses treatment-emergent suicidal ideations and treatment-emergent suicidal behaviors. Each item of the S-STS is scored on a 5-point Likert scale (0 = not at all, 1 = a little, 2 = moderately, 3 = very, and 4 = extremely) and it takes approximately 1 to 2 min to complete. Data from the Sheehan-STS can be analyzed as individual item scores, suicidal ideation subscale score, suicidal behavior subscale score, and total score.

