### Power analysis and sample size calculation

A comparable study published by Khan et al. [26] of a 6-week double-blind trial in 40 patients found a score reduction of 4.8 (SD = 5.1) in the clinician administered S-STS in the placebo group, while a score reduction of 6.7 (SD = 5.8) was found among the lithium group The assumption that all lithium patients achieve a therapeutic serum-level in the current study seems to be reasonable due to the considerable higher lithium dose in comparison with the Khan et al. study. Therefore, these values have been used as estimates for the expected group difference in this study.

With an alpha level of 0.05, and statistical power of 0.8, sample size estimation for a two-sided *t*-test with unequal variances results in a required number of 131 patients per group. Nevertheless, a *t*-test has considerably less power than an analysis of covariance (ANCOVA), which will be used in this analysis. Borm et al. [27] showed for sample size n and a baseline-follow-up correlation rho, that an ANCOVA with (1-rho^2)*n subjects has the same power as the corresponding *t*-test. There is no published data on test-retest correlations of the S-STS to our knowledge; however, a recalculation of data from the “Basis-Studie Kompetenznetz Depression” [28] with 1014 naturalistically treated depressed patients showed correlations from 0.36 to 0.54 for the self-report S-STS between baseline and week 8. Therefore, a conservative assumption of 0.3 for the expected correlation was chosen, which yields a number of 120 patients per group. These patients will form the modified Intention to Treat (ITT) sample including all patients who will be randomized and not discontinue from the study before any efficacy measurement. A rate of approximately 5 % of randomized patients dropping out for any reason before entering the ITT sample is presumed, which results in 127 patients needed to be randomized per group. Therefore, 508 patients will be required to be screened assuming a rate of 50 % of screened patients fulfilling the inclusion criteria. We are expecting good adherence to the intervention as this will not result in major side effects. However, we anticipate that there will be about 5 % loss to follow-up, and this is accounted for in the sample size estimation.

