#### Primary outcome measures

An analysis of covariance (ANCOVA) model will be used to compare the final clinician administered S-STS scores between the groups, including the initial score as a covariate.

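### As written, a death by suicide before week 5 cannot worsen the primary S-STS endpoint: the patient keeps the last rating before the event, or drops out of the analysis set

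*Protocol article*

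**What the plan says.** All references are to the protocol article.

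- **Endpoint.** Methods/Design defines the primary endpoint as the "change in Sheehan Suicidality Tracking Scale (S-STS, [17]) between the beginning of treatment and after a treatment episode of 5 weeks". The hypothesis there concerns suicidal thoughts and/or behavior.
- **Scale.** Under Clinician administered scales: "The eight item scale assesses treatment-emergent suicidal ideations and treatment-emergent suicidal behaviors". Each item is scored 0 to 4.
- **Primary model.** Under Primary outcome measures, an ANCOVA "will be used to compare the final clinician administered S-STS scores between the groups, including the initial score as a covariate".
- **Missing scores.** Under Statistical analysis: "All efficacy outcome measures will be analyzed on an intent-to-treat (last observation carried forward) basis and study completer basis". No exception is named.
- **Analysis set.** Under Power analysis and sample size calculation, the modified ITT sample is "all patients who will be randomized and not discontinue from the study before any efficacy measurement". A rate of about 5% "of randomized patients dropping out for any reason before entering the ITT sample is presumed".
- **Other routes for the event.** Adverse-event proportions are summarized (Statistical analysis). Serious adverse events are documented and a board oversees the trial (Data and safety management). For the C-SSRS, the between-group model names only the items on severity and intensity of ideation (Secondary outcome measures).

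**The concern.** No S-STS rating can follow a death. The carry-forward rule is written for all efficacy measures, so it supplies the rating made before the suicide, as it would for a patient who moved away. The completer analysis leaves the patient out. A death before any efficacy measurement removes the patient from the modified ITT set. None of these routes lets the event count against the arm in which it happened.

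This is not the general objection to carrying observations forward. A mixed model would have the same defect, because it would project a continuing course for someone who died of the condition under study.

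The Background shows why it matters here. In the earlier one-year lithium trial, suicides were 0 of 84 on lithium and 3 of 83 on placebo, while attempts were seven in each arm. The distortion can go either way: a suicide on placebo would be lost as evidence for lithium, and a suicide on lithium would be lost as evidence of harm.

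**Working it through.** **1. The plan's own figures.** Inputs from Power analysis and sample size calculation: reductions 4.8 (SD 5.1) and 6.7 (SD 5.8), two-sided alpha 0.05, power 0.8, correlation 0.3, 5% loss.
- Difference: 6.7 − 4.8 = 1.9. Pooled SD: √((5.1² + 5.8²)/2) = 5.461.
- Unequal-variance t-test: 131 per group gives power 0.801, and 130 gives 0.798. The stated 131 is reproduced.
- ANCOVA: (1 − 0.3²) × 131 = 119.2, so 120. Dropout: 120/0.95 = 126.3, so 127.

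No stated figure is wrong. The point concerns how the endpoint is scored.

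**2. What the stated rules do with a suicide.**

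| Timing | ITT, carried forward | Completers |
|---|---|---|
| After a post-baseline rating | last score before death | absent |
| Before any efficacy measurement | excluded from the modified ITT | absent |

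The second row reads the definition as meaning a post-baseline measurement, since every patient needs a baseline S-STS to enter. If the baseline score counts, it is carried forward and the death is recorded as no change. If the carried score is an average end-of-treatment score, the death is recorded as an improvement of about 5 to 7 points. An early death would carry a score nearer to baseline.

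**3. Expected number.** Assumption: the cited one-year placebo rate applies evenly over 5 weeks.
- 3/83 × 5/52 × 127 = 0.44 placebo suicides.
- Chance of at least one: 1 − exp(−0.44) = 0.36. Chance of none: about 0.64.
- The same calculation for lithium gives 0, from 0 of 84.

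**4. Size per event.** Maximum score as the article describes the scale: 8 × 4 = 32. The carried score L is not given, so 0 to 20 is assumed. Shift in the arm mean at 120 per arm: (32 − L)/120.

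| L | Shift, one event | Share of 1.9 |
|---|---|---|
| 20 | 0.10 | 5% |
| 8 | 0.20 | 11% |
| 0 | 0.27 | 14% |

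Three events in one arm give 0.30 to 0.80 points (16% to 42%). Averaged over the chance of an event, the shift is 0.44 × 0.10 to 0.44 × 0.27, or 0.04 to 0.12 points (2% to 6% of 1.9).

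**5. What a score of 32 inside the ANCOVA would do.** Simulation with 120 per arm, correlation 0.3, 6,000 runs. Assumed: baseline mean 15 and final-score SD 5.461.

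| Events scored 32 | Power |
|---|---|
| none | 0.81 |
| 1 placebo | 0.85 |
| 3 placebo | 0.93 |
| 1 lithium | 0.69 |
| 1 in each arm | 0.75 |

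The one-per-arm row reflects mainly added variance. The expected final means are 15 − 4.8 = 10.2 and 15 − 6.7 = 8.3, so the two deviations are 21.8 and 23.7. The added variance is (21.8² + 23.7²)/240 = 4.3. The residual variance is 5.461² × 0.91 = 27.1. The increase is about 16%.

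**The case against.** The strongest reply is that the article is condensed. Its carry-forward sentence is a general convention that never mentions death, and a full protocol or SAP, not shown here, could hold a special rule. That is possible. But the point rests on what the article states: the rule covers all efficacy measures without exception, so a special rule elsewhere would have to depart from it.

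Three further replies stand in part.

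- **Attempts.** A reader might infer that attempts are lost in the same way. The documents do not support this. No section says that an attempt ends participation or goes unrated, discharged patients continue in the study, and the S-STS covers behavior. If a rating follows the attempt, it is the one carried forward. Scaling the earlier trial's 14 attempts gives about 2 across both arms (14/167 × 5/52 × 254), but that counts all attempts, not those that end participation without a rating.
- **Small size.** On these assumptions no placebo suicide is the likelier result. If suicides fell on placebo, as in the cited trial, the rule would work against the trial's hypothesis and would not produce a false positive. Whether the one-year rate is too low or too high for these inpatients cannot be settled from the article.
- **Visibility.** Suicides would appear in the safety reporting, and C-SSRS behavior and lethality are collected. This limits the chance of a misleading overall report but does not repair the primary score.

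**Conclusion.** The point holds for completed suicide. Under the stated rules the event adds nothing to the primary endpoint, whichever arm it occurs in. Each event would be worth about 0.1 to 0.27 points of an arm mean (5% to 14% of the planned difference) if scored at 32. This assumes 120 per arm and a carried score of 0 to 20. The expected number, 0.44 on placebo, assumes that the cited rate is constant over time.

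Two stronger readings should not be drawn. First, the carried score need not show improvement: it may lie above baseline, and all that follows is that the death itself adds no deterioration. Second, a worst score would not stop an arm with a suicide from showing a mean improvement, because a shift of at most 0.27 points is small beside reductions of 4.8 to 6.7. The defect is that the endpoint ignores an outcome it is meant to cover. It is not that the trial's conclusion is likely to be reversed.

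**What to change.** In Statistical analysis and Primary outcome measures:

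1. State that death by suicide before week 5 is an outcome and not missing data.
2. Keep these patients in the ITT set even without a post-baseline rating. Say which value the ANCOVA then uses, since carrying forward can supply only the baseline score.
3. Prespecify a worst-rank or composite analysis of the final S-STS with suicide ranked worst, as a sensitivity analysis reported beside the ANCOVA. With ranks, one patient among 120 can change the probability that a patient in one arm ranks above a patient in the other by at most 1/120 = 0.8 percentage points, so a single extreme value cannot dominate.
4. If a patient leaves after an attempt and a clinician S-STS covering the event exists, use that rating and not the one before it.

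A score of 32 should not be required in the primary ANCOVA, where one event in each arm would cut simulated power from about 0.81 to 0.75. Nor should it be required in the completer set, to which a deceased patient does not belong.

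The cost is a few sentences and one additional analysis. Treatment, visits and sample size do not change.

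### LOCF for the week-5 S-STS comparison is biased, in either direction, whenever dropout or its timing differs by arm while scores are still falling; the companion completer analysis does not repair this

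*Protocol article*

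**What the plan says.** The Statistical analysis section of the protocol article sets one rule for every efficacy outcome: "All efficacy outcome measures will be analyzed on an intent-to-treat (last observation carried forward) basis and study completer basis". It does not say which of the two bases is confirmatory.

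The primary endpoint is the change in S-STS "between the beginning of treatment and after a treatment episode of 5 weeks" (Methods/Design). The model is an ANCOVA to "compare the final clinician administered S-STS scores between the groups, including the initial score as a covariate" (Primary outcome measures).

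Power analysis and sample size calculation builds the 120 per group on a "modified Intention to Treat (ITT) sample including all patients who will be randomized and not discontinue from the study before any efficacy measurement". It inflates 120 to 127 for about 5% who leave before entering that set. It then adds that "we anticipate that there will be about 5 % loss to follow-up, and this is accounted for in the sample size estimation".

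Mixed regression models for weekly change appear only under Secondary outcome measures. The Methods/Design list of weekly analyses reads "Weekly changes in the C-SSRS, MADRS, HAM-A and YMRS within the observation period" and does not name the S-STS. Intervention/Course schedules weekly visits with psychometric testing, starting three days after baseline.

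**The concern.** LOCF gives a fair week-5 comparison only if scores stay flat after a patient leaves, or if the errors happen to cancel between arms. The plan's own figures point the other way: S-STS is expected to fall by several points in both arms over the treatment period. A patient who leaves early is therefore entered at a score that is too high for week 5. The shortfall depends on how many patients leave and when.

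If rates or timing differ by arm, as could happen with intolerance on lithium or lack of response on placebo, part of the estimated difference reflects dropout and not treatment. This can happen even when lithium has no effect. The completer analysis is no safeguard, because it also selects patients on something that happens after randomisation. At stake are the direction and size of the confirmatory estimate, and the type I error of the test.

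**Working it through.** **Inputs from the document** (Power analysis and sample size calculation): change 4.8 (SD 5.1) on placebo and 6.7 (SD 5.8) on lithium, so the difference is 1.9; two-sided alpha 0.05; power 0.80; correlation 0.3; 5% lost before the modified ITT set.

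**Inputs assumed:** the post-baseline dropout share *p* in each arm; the fraction *f* of the 5-week change already reached at a dropout's last visit; a linear course; dropout unrelated to outcome within arm. The document gives none of these.

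**Step 1: the plan's sample size.**
- Pooled SD = √((5.1² + 5.8²)/2) = 5.46. A t-test with unequal variances at 131 per group has power 0.801.
- ANCOVA: 131 × (1 − 0.3²) = 119.2, so 120. On that variance the standard error is √(0.91 × (5.1² + 5.8²)/120) = 0.673 and power is 0.803.
- 120/0.95 = 126.3, so 127.

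All three figures reproduce. The single 5% step is used up by losses before the modified ITT set. If the 5% loss to follow-up is a separate loss, 120/0.95² = 132.96, so 133 would be needed. Nothing in the calculation allows for a smaller LOCF difference.

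**Step 2: expected LOCF difference.** In an arm with true change *m*, the LOCF change is m × (1 − p(1 − f)). The difference is

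6.7 × (1 − p_L(1 − f_L)) − 4.8 × (1 − p_P(1 − f_P)).

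| Post-baseline dropout (lithium / placebo) | f | Difference | Power at 120 |
|---|---|---|---|
| 0 / 0 | – | 1.90 | 80% |
| 5% / 5% | 0.5 | 1.9 × 0.975 = 1.85 | 78% |
| 5% / 5% | 0.2 | 1.9 × 0.96 = 1.82 | 77% |
| 20% / 20% | 0.5 | 1.9 × 0.90 = 1.71 | 72% |
| 20% / 20% | 0.2 | 1.9 × 0.84 = 1.60 | 66% |
| 20% / 10% | 0.5 | 6.03 − 4.56 = 1.47 | 59% |
| 10% / 20% | 0.5 | 6.365 − 4.32 = 2.05 | 86% |

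With the same timing in both arms, LOCF inflates the difference once placebo dropout exceeds 6.7/4.8 = 1.4 times lithium dropout. Otherwise it dilutes it.

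**Step 3: no true effect** (both arms change by 4.8).
- 30% against 10%, f = 0.5: spurious difference 4.8 × 0.20 × 0.5 = 0.48. The type I error is 11% with SD 5.46 in both arms and 12% with SD 5.1. A simulated LOCF ANCOVA gave 0.48 and 15%.
- Equal 20% dropout with different timing (f = 0.2 against 0.8): 4.8 × 0.2 × 0.6 = 0.58. The type I error is about 15%, or 20% in simulation. Equal rates alone do not protect.

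**Step 4: early improvement instead of linear.** Assume a 7-day half-life and last visits spread evenly over days 3, 7, 14, 21 and 28. The fraction reached is (1 − 2^(−t/7))/(1 − 2^(−5)), that is 0.265, 0.516, 0.774, 0.903 and 0.968, with mean 0.685.
- Equal 20%: 1.9 × (1 − 0.2 × 0.315) = 1.78, power 75%. The same visits with linear change give mean f = 0.417 and a difference of 1.68.
- No effect, 30% against 10%: 4.8 × 0.2 × 0.315 = 0.30, type I error about 8%. Linear change on the same visits gives 0.56.

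**The case against.** The strongest reply is about size. The only loss figures in the document are two statements of about 5%. At 5% equal post-baseline dropout the difference falls by less than 0.1 and power by 2 to 3 points. The marked type I error needs 30% against 10%, or clearly different timing. Early improvement shrinks everything further. All of this stands, and it limits the magnitude. It does not remove the bias, because the validity of the test still depends on dropout behaving alike in both arms.

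Stronger readings are tempting, and the document does not support them:

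- *A reader might infer that the trial will not deliver 80% power.* That depends on assumed dropout and trajectory. If the quoted SDs are SDs of change, the ANCOVA variance factor is (1 + 0.3)/2 = 0.65 and not 0.91; simulated power is then 90.5% without dropout and 85.7% at equal 20%. The cited 4.8 and 6.7 might also come from an LOCF analysis, in which case some dilution is already in the 1.9. Neither can be settled from the article.
- *A reader might infer that LOCF always dilutes the effect.* It can equally inflate it, as Step 2 shows.
- *A reader might infer that a suicide would be carried forward at the preceding score.* The article does not say how deaths are scored, and an article commonly leaves this to the full protocol or SAP.
- *A reader might object to the modified ITT set itself.* Excluding patients without any efficacy measurement is a disclosed, conventional choice, and no bias from it can be quantified here.
- *A reader might take LOCF as the declared sole primary analysis.* That is an inference from the powered set; completers are named beside it without ranking.

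**Conclusion.** The concern holds as a criticism of the missing-data method, with modest and conditional size. The article fixes LOCF and completers for the primary outcome. While scores are still falling, LOCF misstates the week-5 contrast in either direction when dropout or its timing differs by arm, and completers do not correct that.

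The effect is minor if post-baseline dropout is near 5% and balanced. It becomes material from about 15–20%, or with a clear imbalance in rate or timing. It vanishes if scores have already levelled off when patients leave. Every figure beyond the reproduced sample size rests on assumed dropout and an assumed course. The sample-size arithmetic itself is correct.

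**What to change.** Name a single primary analysis: a mixed model for repeated measures on the post-baseline clinician S-STS scores from the study visits, with treatment, visit, treatment-by-visit and baseline S-STS by visit. Make the week-5 contrast the one primary test. Keep LOCF and completers as sensitivity analyses, and add one delta-adjusted multiple-imputation analysis for departures from missing at random. State whether the 5% loss to follow-up is the same 5% already used to go from 120 to 127 or a further loss.

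The cost is SAP wording or a short amendment before unblinding, and a little more analysis work. One point needs confirming: that the clinician S-STS is recorded at the weekly visits. LOCF and the weekly psychometric testing imply it, but the article's list of weekly measures does not name it.

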## Abstract

**Background:**

Lithium has proven suicide preventing effects in the long-term treatment of patients with affective disorders. Clinical evidence from case reports indicate that this effect may occur early on at the beginning of lithium treatment. The impact of lithium treatment on acute suicidal thoughts and/or behavior has not been systematically studied in a controlled trial. The primary objective of this confirmatory study is to determine the association between lithium therapy and acute suicidal ideation and/or suicidal behavior in inpatients with a major depressive episode (MDE, unipolar and bipolar disorder according to DSM IV criteria). The specific aim is to test the hypothesis that lithium plus treatment as usual (TAU), compared to placebo plus TAU, results in a significantly greater decrease in suicidal ideation and/or behavior over 5 weeks in inpatients with MDE.

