### Study population

Patients will be recruited from six psychiatric hospitals (Dresden University Clinic, Dresden Neustadt, Berlin, Bochum, Frankfurt, Göttingen) in Germany. Specifically, patients will be recruited upon admission. All patients meeting inclusion criteria will be informed about the study by one of the investigators. Following informed written consent, randomization will be conducted by a central block design, allocating the participant to one of the two treatment groups. Figure 1 shows the trial time-line.

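### Age and gender enter the model only if a baseline test is significant, so the data choose the confirmatory model and usually leave both covariates out

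*Protocol article*

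**What the plan says.** The general part of the Statistical analysis section states that "Analyses will be adjusted for age and gender when there is a significant difference between the groups at baseline". The same paragraph sets the significance level: "All statistical tests will be two-sided using an alpha level of 0.05". Under Primary outcome measures, an ANCOVA is to "compare the final clinician administered S-STS scores between the groups, including the initial score as a covariate"; age and gender are not mentioned there, and no separate rule takes the primary analysis out of the general one. The Abstract gives the status of the trial: "The primary objective of this confirmatory study is to determine the association between lithium therapy and acute suicidal ideation". Under Study population, "randomization will be conducted by a central block design, allocating the participant to one of the two treatment groups", and no stratification by age or gender is described.

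**The concern.** In a properly randomised trial the null hypothesis of a baseline test is true by design, so a significant result is a chance finding. Whether adjustment is worthwhile depends on how strongly the covariate predicts the final S-STS score, and the rule never considers that. It therefore fails in two ways:

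- A significant imbalance in a covariate unrelated to outcome changes the primary model for no benefit.
- A non-significant imbalance in a prognostic covariate is left in the estimate.

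The stake is a confirmatory analysis whose covariate set is known only after baseline data have been compared by arm, with standard errors that take no account of that selection step.

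The rule is also incomplete. It does not say whether one significant difference brings in one covariate or both. If they enter separately there are four possible primary models: neither, age, gender, or both. Nor does it say in which population the baseline tests are run. The section plans both a last-observation-carried-forward and a completer analysis, so the trigger could fire in one and not the other.

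**Working it through.** **The plan's own sample size.** Inputs from Power analysis and sample size calculation: the cited study "found a score reduction of 4.8 (SD = 5.1) in the clinician administered S-STS in the placebo group", and "a score reduction of 6.7 (SD = 5.8) was found among the lithium group". The difference is 6.7 − 4.8 = 1.9 and the pooled SD is √((5.1² + 5.8²)/2) = 5.461.

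- Unequal-variance t-test, two-sided 0.05: power is 0.798 at 130 per group and 0.801 at 131. This agrees with the article: "sample size estimation for a two-sided *t*-test with unequal variances results in a required number of 131 patients per group".
- ANCOVA with correlation 0.3: 131 × (1 − 0.3²) = 119.2, so 120.
- 5 % early dropout: 120 / 0.95 = 126.3, so 127.

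The figures reproduce. They rest on the initial score alone and do not depend on age or gender.

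**How often the model switches.** Taking the general 0.05 level to apply to the baseline tests, and treating the two tests as independent:

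- P(at least one significant) = 1 − 0.95² = 0.0975.
- P(neither significant) = 0.95² = 0.9025.
- Each covariate taken singly fails its own test in 95 % of trials.

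**Error rate and power.** Simulation with 120 per group, correlation 0.3, SD 5.461, and 12,000 trials per scenario. Age and gender are independent and share the explained residual variance equally. Each is added only if its own baseline test gives p < 0.05. The share of residual variance they explain (R²) is not in the article and is varied as an assumption.

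| Assumed R² | Type I error, rule | Power, initial score only | Power, rule | Power, always adjusted |
|---|---|---|---|---|
| 0 % | 0.054 | 0.805 | 0.803 | 0.800 |
| 5 % | 0.049 | 0.799 | 0.801 | 0.814 |
| 10 % | 0.046 | 0.798 | 0.801 | 0.833 |
| 20 % | 0.044 | 0.802 | 0.810 | 0.880 |

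The model switched in 9.0 to 9.8 % of simulated trials. The Monte Carlo standard error is about 0.002 for type I error, √(0.05 × 0.95 / 12,000), and about 0.004 for power, √(0.8 × 0.2 / 12,000). The 0.054 in the first row is simulation noise: both fixed models also gave 0.054 in that scenario. A repeat run gave type I error of about 0.046 to 0.052 under the rule, and power of 0.796 / 0.798 / 0.808 / 0.809 under the rule against 0.798 / 0.812 / 0.840 / 0.873 with fixed adjustment.

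At R² = 10 %, fixed adjustment gains 0.833 − 0.798 = 0.035 and the rule gains 0.801 − 0.798 = 0.003, roughly a tenth of what is available.

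**A near-miss imbalance.** Take one covariate whose baseline difference just misses significance (z = 1.9).

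- Standardised imbalance: 1.9 × √(2/120) = 0.245.
- Residual SD after the initial score: 5.461 × √0.91 = 5.21.
- Shift in the estimate: √R² × 5.21 × 0.245, which is 0.29 points at R² = 5 % and 0.40 at 10 %, against a planned difference of 1.9.
- With no treatment effect, the test statistic then has mean 1.9√R² and SD √(1 − R²). The chance of |Z| > 1.96 is about 6.5 % at R² = 5 % and 7.9 % at 10 %. These rates are conditional on that imbalance.

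**The case against.** The strongest reply is that the rule is itself prespecified. It names both covariates, and its trigger uses baseline data and allocation, not outcomes, so nobody can pick the more favourable p-value. Averaged over randomisations the unadjusted estimate is unbiased and type I error is not inflated. If anything the rule is slightly conservative when the covariates are prognostic: the unadjusted model is then used only when imbalance is small, so its standard error is a little too large. Planned power of 0.80 holds throughout. The gain forgone is unknown and is nil if neither covariate predicts outcome. Never adjusting would also fix the model and would match the sample-size section. In the cumulative regressions, if the link is logit, added covariates change what the odds ratio means.

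All of this stands as a limit on size. The selection step does not make the test anti-conservative on average, the bias is conditional on the realised imbalance, and 9.75 % is a switching frequency, not an effect on the result. None of it supports the rule, because a test that carries no information on prognostic value still decides the covariate set. The article itself relies on covariate adjustment to go from 131 to 120 per group, so the case for precision is already accepted. Nor is this a detail left to an analysis plan: it is a stated rule that such a plan would inherit.

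**Conclusion.** The concern holds. The covariate set of the confirmatory model is decided by the data: it would change by chance in about 9.75 % of properly randomised trials, and in about 90 % age and gender would be left out whatever their prognostic value. This assumes that the general 0.05 level governs the baseline tests and that the two tests are independent.

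There is no inflation of type I error on average. The loss of power runs from nil (covariates not prognostic) through about 1 percentage point at R² = 5 % and 3 at 10 % to 6 or 7 at 20 %; these R² values are assumptions. The planned sample size is unaffected. The rule should be changed, but the defect does not threaten the validity of the trial.

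**What to change.** Delete the conditional sentence. State that the primary ANCOVA always includes the initial clinician-rated S-STS score, age as a continuous variable, and gender, and that the same two covariates enter the secondary models in all cases, fixed before unblinding. Report the baseline table without significance tests. For the cumulative regressions, say that the reported effect is conditional on these covariates.

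The cost is one sentence and two degrees of freedom: with 240 patients, residual degrees of freedom fall from 237 to 235. Power at 120 per group by normal approximation is 0.806 / 0.814 / 0.826 / 0.846 / 0.865 if age and gender explain 0 / 2 / 5 / 10 / 15 % of residual variance, so the sample size need not rise. Leaving both covariates out in all cases would also fix the model, but it gives up the precision; always including them is the better choice.
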